### Ethics and informed consent

The study will be organized and coordinated by the Henan Provincial People's Hospital. The study protocol complies with Good Clinical Practice standards for drugs and the ethical guidelines specified in the revised Declaration of Helsinki (2013). The Henan Provincial People's Hospital Institutional Review Board has approved the RAINBOW-AF registry (approval number: 2022-0406), and the trial was registered at ClinicalTrials.gov (NCT 05361889). Data extracted from medical records will be de-identified and anonymized before analysis; therefore, informed consent is waived for this study. This study will also follow the STROBE reporting checklist and the Transparent Reporting of a Multivariable Prediction Model for Individual Prognosis or Diagnosis (TRIPOD) reporting guidelines.

### Data collection

Data will be entered into a web-based case report form, enabled with dynamic data reviews for patient features, expected data ranges, and mandatory fields. It will be derived primarily from three different sources: patients' electronic medical records (including demographics, clinical characteristics, medical management, laboratory measurements, imaging parameters, and drug information), the grade level of treating physicians, referring to the clinical expertise or academic background of clinicians, and the availability of NOACs at each hospital. The specific details include participants' sex, age, body weight, lifestyle, comorbidities (such as diabetes, coronary heart disease, and heart failure), history, latest laboratory data, and risk factors for thromboembolism and bleeding. In addition, co-administration of drugs (such as antiplatelet agents and antiarrhythmic therapy), appearances after NOAC treatment (incidence of inappropriate use), the expertise of physicians, and NOAC availability from that institution will also be documented (Table 2).

**Table 2 T2:** Details of data collection.

**Data collection**	**Interpretation**
• Basic information	Participants' sex, age, body weight, marital status, lifestyle (current smoking and drinking status), educational status, place of residence (rural or urban)
• Disease Information	Type of AF, comorbidities (correlate with stroke and bleeding risk, e.g., anemia, MI, PAD), procedures or surgical history (PCI, CABG, or RFCA)
• History	History of thromboembolism and related hemorrhagic events (major bleeding is defined based upon ISTH criteria and incidences apart from major bleeding are considered as non-major bleeding), fall history
• Latest laboratory data	Serum creatinine levels, hemoglobin, bilirubin, liver function (Child-Pugh score), and renal function (CrCl, calculated using Cockroft-Gault formula)
• Co-administration with NOACs	NOAC medication type, antiplatelet agent, interacting combination medications with NOACs, such as antiarrhythmic therapy, itraconazole, ketoconazole, ritonavir, etc.
• Risk factors for thromboembolism (CHA_2_DS_2_-VASc score)	CHA_2_DS_2_-VASc score is a rating of risk for stroke in patients with AF, items of 1 point each for congestive heart failure, hypertension, diabetes mellitus, vascular disease, Age 65–74 years, sex category [female], and 2 points each for a history of a stroke, TIA, or age ≥ 75 years)
• Risk factors for bleeding (HAS-BLED score)	HAS-BLED score is a rating of risk for bleeding in patients with AF, 1 point each for hypertension, abnormal renal/liver function, stroke, bleeding history or predisposition, labile INR, age 65 years or greater, drugs/alcohol concomitantly
• Expertise of prescriber	Cardiologist or not
• NOACs availability from that institution	Some institutions do not have access to certain NOACs, which can influence the NOAC inappropriateness

*AF, atrial fibrillation; MI, myocardial infarction; PAD, peripheral arterial disease; PCI, percutaneous coronary intervention; CABG, coronary-artery bypass grafting; RFCA, radiofrequency catheter ablation; ISTH, International Society of Thrombosis and Hemostasis; CrCl, creatinine clearance rate; TIA, transient ischemic attack; INR, international normalized ratio; NOAC, non-vitamin K antagonist oral anticoagulant*.

### Evaluation of the appropriate NOACs use

Different nations do not always adopt the standard indications for NOAC prescription. Local policies, such as formulary committees, regulatory approval, and cost-effectiveness, all influence NOAC labeling recommendations (23). In this study, we will adopt an adaptive design to account for a summary of product characteristics, and analyze prevalent NOAC strategies based on indications, NOAC selection, or dosages (Figure 2). We use the recommendations given by NMPA for each agent and the 2021 European Heart Rhythm Association (EHRA) practical guide on the use of NOACs for patients with AF (24). Patients for whom the selected NOAC was contraindicated can be categorized as inappropriate use. If there exist no absolute contraindications, the protocol can evaluate appropriateness according to patient-specific features, like age, weight, renal function, Child-Pugh classification, specific drug–drug interactions, hemoglobin level, and bleeding risk. In cases of discrepancy between the EHRA recommendations and the NMPA recommendations, we adopt the NMPA-approved label recommendations as the standard for determining the appropriateness (Table 3). Patients will be classified as either (a) NOAC-appropriate (rational use of NOAC according to the standardized criteria) or (b) NOAC-inappropriate (irrational use of NOAC according to the standardized criteria).

**Figure 2 F2:**
[figure not shown]
NOACs evaluation flowchart. NOAC, non-vitamin K antagonist oral anticoagulant; DDI, drug-drug interaction; NMPA, National Medical Products Administration; EHRA, European Heart Rhythm Association; AF, atrial fibrillation.

**Table 3 T3:** Approved dosing regimens for the NOACs package inserts for NVAF in the Mainland China.

**Medication**	**Regulations from the NMPA (Mainland China)**
	NMPA (Mainland China) (Revised: 06/2020)
Dabigatran	• Full dose: 150 mg twice daily
	• 110 mg twice daily, if: -age ≥ 80 years -concomitant verapamil
	• Daily dose of 300 mg or 220 mg according to an individual evaluation of the thromboembolic risk and bleeding risk: -age 75–80 years -moderate renal impairment (CrCl 30–50 mL/min) -gastritis, esophagitis, or gastroesophageal reflux -other increased bleeding risk ^a^
Rivaroxaban	NMPA (Mainland China) (Revised: 07/2020)
	• Full dose: 20 mg once daily with food when CrCl ≥ 50 mL/min
	• 15 mg once daily with food, if: -CrCl 15 – 49 mL/min
Apixaban	NMPA (Mainland China) (Revised: 02/2019)
	• Not approved
Edoxaban	NMPA (Mainland China) (Revised: 07/2021)
	• Full dose: 60 mg once daily
	• 30 mg once daily with one or more of the following clinical factors: -CrCl 15 – 50 mL/min -body weight ≤ 60 kg -concomitant use of the following P-gp inhibitors: ciclosporin, erythromycin, dronedarone, or ketoconazole

NVAF, non-valvular atrial fibrillation; NOAC, non-vitamin K antagonist oral anticoagulants; NMPA, National Medical Products Administration; P-gp, P-glycoprotein; CrCl, creatinine clearance rate.

a : Other increased bleeding risks include: Strong P-gp inhibitors; mild to moderate P-gp inhibitor co-medication (e.g., quinidine, verapamil, ticagrelor, and amiodarone); low body weight (<50 kg); acetylsalicylic acid (ASA) and other platelet aggregation inhibitors, e.g., clopidogrel; selective serotonin norepinephrine re-uptake inhibitors (SNRIs), selective serotonin re-uptake inhibitors (SSRIs), and non-steroidal anti-inflammatory drugs (NSAID); other medicinal products that may impair hemostasis; functional platelet defects or thrombocytopenia; major trauma and recent biopsy; and bacterial endocarditis.

Since apixaban has not been fully studied in Chinese populations, the NMPA did not approve the NVAF indication for apixaban; thereby, we have excluded it from this study. Rivaroxaban, given 15 mg daily (or 10 mg, based on creatinine clearance rate [CrCl]), in combination with clopidogrel, was also used in patients with AF and recent percutaneous coronary intervention (PCI) or acute coronary syndromes (ACS) in the PIONEER AF-PCI trial. Therefore, we considered that both doses are appropriate for such patients in our study. The NMPA recommends a daily dose of 220 mg for dabigatran, which can be given to patients with CrCl 30–50 ml/min, aged ≥75 years, or with increased bleeding risk. The NOAC prescription was deemed reasonable for patients aged ≥75 years.

### Quality control

Standard criteria for NOAC appropriateness were drafted by the two highly experienced pharmacists ([name] and [name]) after obtaining consent from all collaborators. A steering committee, comprising of an independent panel of experts (organized by [name]) blinded to RAINBOW-AF data independently checked the entire algorithm program (including recommendation-consistency, under-dosing, or over-dosing) to validate its results. A standard electronic data capture form was devised to accumulate data. To explain each data element as clearly as possible, consensus must be met prior to the entry of study data to discuss the specifics. RAINBOW-AF health personnel who are involved in the care of the study participants will receive rigorous training with periodical quality control inspection prior to the study. All study outcomes are defined based on the diagnosis at the first discharge to avoid misclassification. Manual chart review results must conform to the program of the algorithm revealed above in all cases. Data monitoring will be implemented by the coordinating administrators to determine the integrity and accuracy of data input.

### Primary outcomes

The primary outcomes include (a) profiles of NOAC use in the elderly; (b) the rate of inappropriate NOAC use according to the guidelines and labeling recommendations; (c) potential risk factors related to inappropriate NOAC use; and (d) creation of a prediction model for inappropriate NOAC use. First, we will try to identify the characteristics of participants who were given appropriate NOAC agents and those who were not from a number of several variables (e.g., demographics, clinical, management, expertise of treating clinicians, NOAC availability, and the prevalence of potentially inappropriate NOAC use). Next, using this binary outcome, a logistic model will be fitted to quantify risk factors correlated with these variables with selections of NOAC-inappropriate regimens. Lastly, we will create a prediction model using both logistics and machine learning method for predicting inappropriateness in the entire cohort.

### Sample size calculation

This study is designed as a multicenter cross-sectional study. Assuming that each institution can treat 300–500 patients with AF per year, patients over 75 years old account for 20–30% and the rate of NOAC use is ~50–70%, with a 2% error range and 95% confidence interval (CI). The drop-out rate is not considered in the calculation as the primary outcomes will be evaluated during hospitalization; the drop-out rate is expected to be very low. To get a representative result, we calculated that a sample size of 1,500 patients would be sufficient. Since this is an event-driven study (the rate of inappropriate NOAC use), the total number of patients may change as necessary according to the cumulative number of target events.

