Previous studies report relevant risk factors for inappropriate NOACs use. In the SAGE-AF (Systematic Assessment of Geriatric Elements in Atrial Fibrillation) cohort, a potentially inappropriate NOAC dose was prescribed to nearly a quarter of older adults. This stemmed from patients being older, having poor renal function, and higher CHA_2_DS_2_-VASc scores (16). Another Korean study found that NOAC label adherence was approximately 60%, and the risk factors of NOAC under-dosing were independently related to old age (≥75 years), female sex, lower body weight (< 60 kg), renal impairment (CrCl < 50 ml/min), hypertension, previous stroke/transient ischemic attack (TIA)/thromboembolic events, bleeding history, and concomitant dronedarone or antiplatelet agent use (29). In the ORBIT-AF II registry (18), compared with those whose NOAC dose was appropriately reduced, patients accepting inappropriate dose reductions were younger and had lower bleeding risk scores. Physician assessment may have a strong impact on inappropriate NOAC dosing; however, there may also be drug-specific factors. In Mainland China, information on practice patterns of NOAC administration and the use of NOACs for licensed indications in older patients remains scarce.

Currently, few studies have focused attention on the prediction model of the risk factors of NOAC inappropriateness in elderly patients with AF. Considering that inappropriate NOACs doses are prescribed to a fair percentage of older patients with AF, with most being under-dosed, the development of a practical prediction model with reliable predictability is of great value. To our knowledge, this will be the first study to establish a feasible prediction model for predicting inappropriate NOAC use in older Chinese patients with AF. In the prediction model of probabilistic estimation, we will combine the above independent predictors and the risk factor variables from previously published research. Accordingly, we believe that the prediction model could be applied as a simpler and more effective tool for clinical decision-making for elderly patients with AF.

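### At the NOAC-use and inappropriate-use rates the protocol quotes, 1,500 patients do not give the stated ±2 points at 95% confidence, and the proportion being estimated is not among the inputs

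*Protocol article*

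**What the plan says.** The Sample size calculation section gives three quantities, the last of them together with its precision target: 300–500 AF patients per institution per year; "patients over 75 years old account for 20–30" per cent; and "the rate of NOAC use is ~50–70%, with a 2% error range and 95% confidence interval (CI"). No allowance is made for drop-out. The result is that "we calculated that a sample size of 1,500 patients would be sufficient". The same paragraph then calls the study event-driven, so that "the total number of patients may change as necessary according to the cumulative number of target events". No number of events is given.

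The Primary outcomes section lists the rate of inappropriate NOAC use as outcome (b). The only values for such a rate in the article are background figures in the Discussion. In one cohort, "a potentially inappropriate NOAC dose was prescribed to nearly a quarter of older adults". In a Korean study, "NOAC label adherence was approximately 60" per cent, which implies about 40% non-adherence.

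**The concern.** A precision calculation needs the proportion to be estimated, a margin and a confidence level. The margin and the level are stated, but the proportion is not. Site volume, age share and NOAC-use rate together describe how many eligible patients the sites can supply. The NOAC-use rate cannot stand in for the target proportion, because the Data sources section restricts the study to patients receiving a NOAC, so within the cohort that rate is 100% by design.

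When the quoted rates are put into the usual formula, the result is well above 1,500. The ±2-point margin is the only statistical property the article claims for its sample size, so a reader relying on it would expect a somewhat tighter planned precision than 1,500 patients provide at the rates the article cites.

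**Working it through.** **Inputs.** Margin d = 0.02, read as an absolute half-width, and 95% confidence, taken as two-sided (z = 1.96), both from Sample size calculation. NOAC-use rate 50–70%, same section. Inappropriate-use rate about 25% and about 40%, from the Discussion. Stated size 1,500. Number of hospitals 31, from Data sources.

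**Step 1: try to reproduce 1,500.** n = z²p(1−p)/d² = 3.8416·p(1−p)/0.0004 = 9,604·p(1−p). The half-width at 1,500 is 1.96·√(p(1−p)/1,500).

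| Proportion p | Where it comes from | n for ±2 points | Half-width at 1,500 |
|---|---|---|---|
| 25% | inappropriate use, cohort in Discussion | 1,801 | ±2.19 |
| 40% (or 60%) | complement of adherence in Discussion | 2,305 | ±2.48 |
| 50% | NOAC use, lower end | 2,401 | ±2.53 |
| 70% | NOAC use, upper end | 2,017 | ±2.32 |

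Reading the cohort figure as 23% rather than 25% gives 9,604 × 0.1771 = 1,701 patients, or ±2.13 points at 1,500. The stated size is not reproduced at any of these rates.

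**Step 2: find what 1,500 does fit.** Setting p(1−p) = 1,500 × 0.0004/3.8416 = 0.1562 gives p = 19.4% or 80.6%. So 1,500 meets ±2 points only at 19.4% or below, or 80.6% or above. At 20% the formula gives 1,537, which is close, but in this section 20% is the lower end of the share over 75, not a rate of NOAC use or of inappropriate use.

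**Step 3: other readings of the margin.**
- 2% as the total width of the interval (d = 0.01): 7,203 at 25%.
- 2% as a relative error: 28,811 at 25%, and still 4,116 at 70%.
- A one-sided 95% limit: 1,269 at 25%, 1,624 at 40%, 1,691 at 50%. The article states no one-sided interval, and this reading still misses at 40% and 50%.
- A margin of 2.5 points: 1,476 at 40% and 1,537 at 50%. This is the margin that 1,500 roughly supports at those rates.

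**Step 4: finite population correction.** The paragraph's own volumes imply a yearly pool of NOAC users over 75 of 31 × 300 × 0.20 × 0.50 = 930 to 31 × 500 × 0.30 × 0.70 = 3,255. Corrected to the largest pool at the worst case p = 50%, n = 2,401/(1 + 2,400/3,255) = 1,382. On that reading 1,500 would be enough. No such correction is stated, and the Site selection section aims at a sample representative of NVAF patients in mainland China, not at one year's patients in the 31 hospitals.

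**Step 5: clustering, for illustration.** The mean cluster size is 1,500/31 = 48.4. The design effect is 1 + (48.4 − 1)·ICC. The documents give no ICC, so these values are assumptions:
- ICC 0.01: design effect 1.47, half-width ±2.7 at 25% and ±3.0 at 40%.
- ICC 0.02: 1.95, ±3.1 and ±3.5.
- ICC 0.05: 3.37, ±4.0 and ±4.6.

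Table 2 gives a reason to expect an ICC above zero: it notes that access to certain NOACs differs between institutions and may affect inappropriateness.

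**The case against.** The strongest reply is that the article shows neither a formula nor a planning rate, and an article may leave both to the full protocol. The 25% and 40% are background figures that the sponsor never names as planning values. The 40% is a complement taken from a Korean label-adherence study, while this study applies its own appropriateness standard. A planned rate of 19.4% or less would reconcile 1,500 with ±2 points, and a finite population correction would do so at every rate. This stands in part: one cannot say that no assumption yields 1,500, or that the true rate will not turn out low enough. It does not remove the point. The section presents inputs, a precision and a calculated result that do not agree, it does not mention the rate that would make them agree, and the finite population reading runs against the stated national inference.

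Three stronger readings are tempting, and the documents do not support them.
- A reader might infer that the prevalence will be published with false precision. The reported interval will be computed from observed data, whatever margin was planned.
- A reader might take ±3 points or more as the study's real precision. That rests entirely on an assumed ICC.
- A reader might call the event-driven sentence incompatible with a precision-based size. Extending a base size to accrue events for the prediction model, also a primary outcome, is coherent. What is missing is a link to that purpose and a number, and the number may sit in the full protocol.

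**Conclusion.** The point holds, with moderate severity. As written, 1,500 does not follow from ±2 points at 95% confidence at any NOAC-use or inappropriate-use rate the article quotes, and the proportion to be estimated is absent from the listed inputs. Before clustering, the planned half-width is larger than stated by about 0.2 points at 25% and 0.5 points at 40–50%.

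This rests on a two-sided interval, an absolute margin, independent patients and inference beyond the 31 hospitals. Clustering would widen the interval further, but by how much cannot be determined from the documents. The error is confined to the planning claim: it does not bias the estimate, and the article ties no power statement to this calculation. The open-ended event sentence is a secondary matter of clarity.

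**What to change.** Keep 1,500 and correct the statement around it.

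1. Name the anticipated rate of inappropriate NOAC use as the planning proportion, give its source, and state the formula. Present site volume, age share and NOAC-use rate as feasibility figures.
2. Restate the precision at 1,500 as about ±2.2 points at 25% and ±2.5 points at 40–50%, assuming independent patients.
3. Say that clustering within the 31 hospitals will widen this, for example to about ±3.1 points at 25% if the ICC were 0.02, labelled as an assumption. Have the reported confidence interval allow for hospital.
4. Delete the event-driven sentence, or tie it to a stated event target for the prediction model.

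The cost is wording, plus an interval that accounts for hospital. No extra patients are needed, though the stated precision becomes slightly less favourable. If ±2 points is truly required, about 1,800 to 2,400 patients would be needed before any allowance for clustering.

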### Statistical analyses

Categorical data will be presented as frequencies and be compared by Chi-squared or Fisher's exact test as appropriate. Continuous data will be reported as mean ± standard deviation or median and interquartile range (IQR) and analyzed by either Student's *t*-test or the Mann–Whitney *U* test. In this study, data will be extracted and summarized using Excel 2016. Univariate and multivariate logistic regression analyses will be applied to ascertain the correlation between candidate variables and NOAC inappropriate use. Multicollinearity between the variables will be shifted based on the variance inflation factor (VIF; VIF > 5 is considered strong collinearity) (25). Two criteria will be considered necessary for a variable to be incorporated into the final prediction model: (a) a univariate *p-*value indicative of NOAC prescription inappropriateness ≤0.05 and (b) a plausible connection with risk factors from NOAC inappropriate prescriptions based on previously published research. The risk tendency of inappropriate NOAC use among risk stratifications will be evaluated by the Cochran-Armitage trend test (26). Machine learning algorithms will be built based on the Scikit-learn package (version 0.22.2). Interaction analyses will be used to compare predictive performance between machine learning models. Statistics will be performed employing STATA software (version 12.0, Stata Corporation LLC, College Station, United States), and a *p* < 0.05 will be considered to be statistically significant.

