### Strengths and limitations

The main strengths of this study are believed to be as follows: First, we will include data from a national, comprehensive, and diversified cohort of older patients with AF and will perform in-depth phenotyping of NOAC use to help refine best practices for older adults with AF. Second, most studies evaluating the appropriateness of NOAC primarily focus on dosage in the general population, while our study will evaluate the rationale of NOAC decision-making for older adults from multiple perspectives: patient factor (patients' demographics and categories of treating physicians) and institution layer (the availability of certain NOACs in that center). Additionally, this study will build the first prediction model to predict the inappropriateness of NOAC in older Chinese patients with AF.

Inevitably, this study has some inherent limitations. First, due to the inherent restriction placed by its design, this study will not evaluate the outcomes of older adults with AF treated with inappropriate anticoagulation therapy, nor will there be a follow-up for efficacy evaluation. Nevertheless, its primary purpose is to establish a reliable prediction model in older adults with NVAF receiving NOAC. Second, data will be dependent on the quality of medical record extraction, so that residual and unmeasured covariates among the associated variables may influence the results, even after strict measurement and recording of crucial variables and avoidance of confounding factors. Last, the prediction model needs independent validation in other cohorts to establish its utility for clinical use, not least in older outpatients taking NOACs.

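### The 1,500 patients are not sized for the prediction model that the protocol calls its primary purpose, and the stated p-value entry rule puts the logistic model at material risk of overfitting

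*Protocol article*

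**What the plan says.** - **Size.** The Sample size calculation section gives site throughput, the share of patients over 75, a statement that "the rate of NOAC use is ~50–70" per cent, a 2% error range and a 95% confidence interval. It then concludes that "we calculated that a sample size of 1,500 patients would be sufficient". It also says that "the total number of patients may change as necessary according to the cumulative number of target events", but sets no target number. It states no expected rate of inappropriate use, no number of predictors and no performance target.
- **Purpose.** Primary outcomes lists the prediction model as item (d). Strengths and limitations goes further: "its primary purpose is to establish a reliable prediction model in older adults with NVAF receiving NOAC".
- **Development data.** Data separation and feature filtering assigns patients 8:2 to training and test sets.
- **Method.** Statistical analyses states: "Univariate and multivariate logistic regression analyses will be applied to ascertain the correlation between candidate variables and NOAC inappropriate use". A variable needs two things to enter the final prediction model: a univariate p-value of 0.05 or less, and a plausible link in published research. No shrinkage is mentioned.
- **Evaluation.** The section on machine learning models lists AUROC, precision, recall, F1 score and accuracy.

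**The concern.** A sample that estimates one proportion well need not be large enough to develop a multivariable risk model. The model's requirement depends on the number of candidate parameters, the event rate and the signal in the predictors, and none of these enters the justification for 1,500. Selecting on univariate p-values in the same data does not remove the cost of having examined the other candidates, and it tends to keep effects that look large by chance.

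Calibration is at stake. An overfitted model gives risks that are too high for high-risk patients and too low for low-risk patients, so its calibration slope in new patients is below 1. The Discussion presents the model as a probability estimate to support clinical decisions, so this kind of error matters. The five planned measures describe discrimination and classification and would not show it.

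**Working it through.** **1. The plan's own figure.** For one proportion, n = z²p(1−p)/d², with z = 1.96 and d = 0.02.

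| p | n |
|---|---|
| 0.5 | 2,401 |
| 0.6 | 2,305 |
| 0.7 | 2,017 |

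The stated 50–70% therefore does not give 1,500. That rate is also NOAC use, not inappropriate use. The formula gives about 1,500 only for p near 0.19–0.20 (1,479–1,537), a rate the document does not state.

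**2. Inputs for the model.**
- Development set: 0.8 × 1,500 = 1,200 (Data separation and feature filtering).
- Event rate: not stated. The Discussion cites one cohort with nearly a quarter inappropriate and one study with about 60% label adherence. I take 25% and 40% as the range.
- Candidates: not stated. Items named in Data collection and Table 2, before dummy coding: basic information 8, AF type and named comorbidities 7, procedures 3, history 4, laboratory 5, NOAC type and co-medication groups 4, risk scores 2, prescriber specialty and grade 2, NOAC availability 1. Total 36.
- Nagelkerke R²: not stated. I show 0.15 to 0.30.
- Target shrinkage: S = 0.90, a conventional choice.

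**3. Events per candidate.** 0.25 × 1,200 = 300 and 300/36 = 8.3. 0.40 × 1,200 = 480 and 480/36 = 13.3.

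**4. Parameters supported.** The maximum Cox–Snell R² at event rate φ is 1 − exp{2[φ ln φ + (1−φ) ln(1−φ)]}, which is 0.675 at 25% and 0.740 at 40%. Then R²cs = Nagelkerke R² × maximum, and the supported number of parameters is n(S−1) ln(1 − R²cs/S).

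Example (25%, R² 0.15): R²cs = 0.15 × 0.675 = 0.101, and 1,200 × (−0.1) × ln(1 − 0.101/0.9) = 14.3.

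Solving the same equation for S with 36 parameters gives the expected shrinkage.

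| Nagelkerke R² | Parameters supported by 1,200 (25% / 40% events) | Shrinkage with 36 parameters (25% / 40%) |
|---|---|---|
| 0.15 | 14.3 / 15.8 | 0.78 / 0.80 |
| 0.20 | 19.5 / 21.6 | 0.83 / 0.84 |
| 0.25 | 24.9 / 27.6 | 0.86 / 0.87 |
| 0.30 | 30.6 / 34.0 | 0.885 / 0.895 |

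All 36 are supported at R² of about 0.345 (25%) or 0.315 (40%).

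**5. Effect of the stated entry rule.** I simulated univariate screening at p ≤0.05 among 36 candidates in 1,200 patients, followed by ordinary logistic regression. Mean calibration slopes were about 0.59–0.93, depending on how the signal is spread. With 25% events and R² about 0.14, the slope was about 0.84 when ten moderate effects carried the signal and 0.62 when many weak ones did. A ridge penalty tuned by cross-validation gave about 1.0 on average. Screening therefore does not reliably remove the problem, and it makes it worse when effects are many and weak.

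**The case against.** **R² may be higher than 0.15.** Inappropriateness is assigned by label rules that use age, weight, renal function and interacting drugs, and all of these are collected. If R² exceeds about 0.32–0.35, the shortfall disappears. This stands, and it is why the result is given as a range.

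**The candidate count is mine.** Table 2 lists data items, not model terms. The collinearity check could drop overlapping items, such as creatinine and creatinine clearance, without reference to the outcome. The published-evidence criterion is also independent of the data. The Discussion names only about 11 factors, which 1,200 patients would support even at R² 0.15. This stands in part: applied strictly and first, that criterion would largely solve the problem. But the protocol fixes neither the list nor the order, and it still requires the p-value.

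**No text says unpenalised.** This is correct. Penalty settings could be in a fuller document, and logistic regression is one of several learners chosen by AUROC. The point is therefore limited to the logistic model and to the entry rule actually stated. A light fixed penalty would not be enough: in one simulation it moved the slope only from 0.72 to 0.74.

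**Other safeguards.** The protocol has a test set, concedes the need for independent validation, and allows the total to change with target events. The first two can detect overfitting but do not prevent it, and the listed measures omit calibration. The third sets no number.

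**A stronger reading.** A reader might infer that the data support under half the candidates and that the model will be overfitted. The documents do not support this. On 1,200 patients, under half (18 of 36) holds only below R² of about 0.19 (25% events) or 0.17 (40%), and certainty would need a candidate count and R² that are not given.

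**Conclusion.** The point holds in conditional form. The document shows that 1,500 is justified only by precision inputs, that no event target is set, and that a reliable prediction model is called the primary purpose. The size of the risk depends on assumptions. With about 36 candidates and 25–40% events, the training set supports about 14–16 parameters at R² 0.15 and 25–28 at R² 0.25, with expected shrinkage of about 0.78–0.90 for R² 0.15–0.30. That is a material risk of overfitting the logistic model, not a certainty. It vanishes if R² exceeds about 0.32–0.35 or if the candidate list is cut beforehand to what the data support.

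A reader might also infer that 1,500 is at least the correct figure for the rate. The stated inputs do not reproduce it for that purpose either.

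**What to change.** No additional patients are needed.

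1. **Statistical analyses:** for the logistic prediction model, replace the univariate p ≤0.05 entry rule with a candidate list fixed in advance from published evidence. Fit it by penalised likelihood (ridge or elastic net), with the penalty tuned by cross-validation within the training data.
2. **Model evaluation:** add the calibration slope, with its confidence interval, to the five listed measures. At 25–40% events the 300 test patients contain only 75–120 events, so the interval will be wide.
3. **Sample size calculation:** state that 1,500 was not derived for the prediction model. Give the number of parameters that the 1,200 training patients support under declared event-rate and R² assumptions, for example about 14–16 at R² 0.15 and 25–40% events. Do not write that 1,500 was derived for the rate unless inputs that yield it are supplied.

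The cost is a change of wording and a different fitting procedure. Some weak candidates are lost and the coefficients are shrunk, so odds ratios for the risk-factor aim should be reported from a separate model.
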